### Collection and screening of health education materials

2.7

#### Sources of health education materials

2.7.1

The health education materials for this study will be sourced from both domestic and international databases, such as WeChat, Wikipedia, doctor Q&A platforms, and ZhiNET, and will include both video and graphic formats. The educational materials, including medical records, will be scientifically accurate and sourced from Baidu documents or relevant literature with appropriate references.

#### Screening of healthy materials

2.7.2

After the health education materials are collected and organized, experts in Brucella research will review the content according to predefined criteria. These criteria will include scientific accuracy, clarity, relevance to brucellosis management, and comprehensiveness. Experts will assess the materials for the following factors:

(1) *Scientific accuracy*: the materials must present information that is consistent with current scientific understanding and clinical guidelines on brucellosis.(2) *Clarity and comprehensibility*: materials should be written clearly and be accessible to the target population, including individuals with varying health literacy levels.(3) *Relevance*: the materials must address key aspects of brucellosis management, including disease awareness, prognosis, self-management strategies, and prevention methods.(4) *Credibility*: sources must be reliable, such as peer-reviewed literature, trusted health organizations, or recognized medical professionals.(5) *Multimedia appropriateness*: visual and video materials must be of high quality, informative, and easy to understand for patients.

After the review, experts will suggest necessary modifications to improve the content. Only high-quality materials meeting these criteria will be included in the study’s health education database. The materials will be categorized into sections such as disease awareness, prognosis, and other aspects of care. These materials will be used to create personalized push recommendations for patients. The push database will include article titles, relevant links, sources, material types, and other pertinent information (54).

### Outcomes measure

2.8

Medical staff will distribute the questionnaire via the Questionnaire Star web platform. Patients will complete it online, receiving instructions either in person (during hospitalization) or by phone (after discharge). Demographic information will be collected through the case system and self-designed questionnaires (Table 1).

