#### Mobile health intervention group

2.5.1

Health education in the mobile health intervention group will be delivered via the WeChat platform on smartphones. The physician or nurse will use WeChat’s messaging function to communicate with the patient promptly. The physician or nurse will address the patient’s concerns promptly. The physician or nurse can also intervene in patient care promptly through the WeChat platform (49).

To ensure high-quality delivery of the intervention, the professionals involved in delivering health education through WeChat (physicians and nurses) will need to meet the following criteria:

Physicians must hold a valid medical degree in general practice or a relevant specialty and have at least 2 years of experience in patient care.Nurses must be licensed and have at least 1 year of experience in patient education or health promotion.All professionals must undergo a brief training program on the HAPA model, the principles of mobile health interventions, and effective communication through digital platforms like WeChat.

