###### Action self-efficacy

2.5.1.1.1

(1) Purpose: to help patients develop initial self-efficacy and motivation to change their health behaviors.(2) Measures: each patient will receive a booklet titled “Health Education for Patients with Brucellosis.” While distributing the booklet, the physician will explain common issues, encourage a positive approach to the disease, and guide patients to actively improve their health behaviors (31). During the initial consultation, physicians will add patients’ WeChat contact information and categorize them for follow-up health education. For patients with low health awareness, physicians will promptly discuss reasons for the lack of awareness, help identify solutions, and encourage mutual communication between patients and physicians.

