###### Action plan

2.5.1.2.1

(1) Purpose: enhance patients’ self-efficacy for maintenance(2) Measures: patients will receive 10-min health guidance from the physician via WeChat every Monday. The physician will help patients develop a long-term health behavior improvement plan and provide daily reminders via WeChat. The content of health education topics will be based on multimedia, in the form of articles, pictures, or videos sent to the advance WeChat group. For patients with low adherence, physicians will emphasize the dangers of neglecting animal husbandry hygiene, the risks of infectious diseases, and the benefits of maintaining hygienic habits and adhering to medication schedules. For patients with moderate adherence, physicians will focus on praise and encouragement to help maintain their confidence. For patients with high adherence, physicians will focus on monitoring their progress. Physicians will proactively seek recovery progress from all patients, guide them on the correct use of medication, and encourage active cooperation in treatment. The physician will encourage all patients to fill out the “Health Behavior Diary,” documenting daily health behaviors, issues, and experiences encountered. Patients will also be encouraged to communicate with the physician promptly, and their health behavior progress will be regularly evaluated.

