##### Data collection

2.10.1.1

All study results, including clinical and laboratory data, will be recorded in the participants’ medical records and case report forms (CRFs). The researchers are responsible for ensuring that all sections of the CRFs are accurately filled out, and that each piece of information can be verified against source data. Each completed CRF must be dated and signed. Data collection will be carried out by trained research staff, who will adhere to standard operating procedures (SOPs) to ensure the accuracy and consistency of the data. All data will be collected in strict accordance with the research protocol approved by the ethics committee. Participants’ personal information and data will be kept strictly confidential, and all records will use identification numbers instead of personal identifying information.

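### Section 2.8 gives the self-report questionnaires to medical staff without separating them from the physicians and nurses who coach only the mHealth arm, so arm-specific over-reporting cannot be excluded

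*Protocol article*

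**What the plan says.** On collection, section 2.8 (Outcomes measure) states "Medical staff will distribute the questionnaire via the Questionnaire Star web platform". It continues: "Patients will complete it online, receiving instructions either in person (during hospitalization) or by phone (after discharge"). Filling in the form is therefore an online act by the patient, but live staff contact goes with it. Section 2.10.1.1 (Data collection) describes the task differently: "Data collection will be carried out by trained research staff". It does not say whether these staff are independent of treatment.

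On coaching, section 2.5.1 gives the WeChat programme to physicians and nurses. Section 2.5.1.1.1 singles out low awareness: "For patients with low health awareness, physicians will promptly discuss reasons for the lack of awareness". Section 2.5.1.2.1 (Action plan) works by level of adherence. At the low level, "For patients with low adherence, physicians will emphasize the dangers of neglecting animal husbandry hygiene". At the next, "For patients with moderate adherence, physicians will focus on praise and encouragement to help maintain their confidence". At the high level the physician monitors progress. The same section says of patients that "their health behavior progress will be regularly evaluated".

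The control arm (section 2.5.2) receives a brochure and telephone follow-up, which also covers adherence to instructions. No graded praise or correction is described there.

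Section 2.2 says that evaluators know the allocation. The Discussion lists social desirability and recall bias as limitations of self-report in general, not as something that may differ between the arms.

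**The concern.** The behaviour primary outcome (section 2.8.1.1) is a self-rated frequency scale covering protective measures with livestock, pen cleaning and hand hygiene. The coaching in section 2.5.1.2.1 covers much the same ground. If a patient believes that the form goes back to the professionals who have been praising or correcting that behaviour, there is a motive to answer favourably. That motive exists mainly in one arm.

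Over-reporting confined to one arm looks the same as an intervention effect. Randomisation, intention-to-treat analysis and multiple imputation do not reduce it, because the answers themselves are wrong. The independent statistical team of section 2.10.1.4 comes in after the answers exist.

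This is separate from whether participants can be blinded. An open-label trial can still keep outcome collection away from those who deliver treatment.

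**Working it through.** **Setting the sections side by side**

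1. *Who collects.* Section 2.8 names medical staff and section 2.10.1.1 names research staff. The two can be reconciled (one sends the link, the other handles data), but neither excludes the coaches.
2. *Who coaches.* Physicians and nurses (section 2.5.1), in the mHealth arm only. They belong to the professional group named in section 2.8.
3. *What separates the roles.* Sections 2.10.1.1 to 2.10.1.3 provide for confidentiality, identification numbers, restricted access and a data management team. None says that intervention staff are outside the authorised group.
4. *Which outcomes are exposed.* The behaviour scale and the self-report secondary scales. Knowledge items (section 2.8.1.2) are marked right or wrong, so a wish to please cannot produce a correct answer.
5. *When.* The intervention lasts 3 months (section 2.1), and Table 1 schedules questionnaires at Months 0, 3, 6, 9 and 12. Month 0 is baseline. Only Month 3 is a post-baseline assessment within the coaching period. A residual effect at Months 6 to 12 is possible but weaker.

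**Sensitivity illustration**

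The plan has no figure on this point to reproduce. From section 2.4: control rate 60%, 29 per arm randomised, 23 per arm after losses. Assumed: no true effect, and a share *f* of mHealth non-adopters who report a score above the cut-off of 70, over and above any such share among controls.

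- Reported mHealth rate: p₁ = 0.60 + 0.40 × *f*. Control: p₂ = 0.60.
- Test: z = (p̂₁ − p̂₂) / √[p̄(1 − p̄) × 2/n], rejecting if |z| > 1.96 (two-sided 5%).
- False-positive rate: the sum of the products of the two binomial probabilities over all pairs of counts for which the test rejects.

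| *f* | p₁ | n = 29 per arm | n = 23 per arm |
|---|---|---|---|
| 0 | 0.60 + 0.40 × 0 = 0.60 | 4.6% | 5.1% |
| 0.10 | 0.60 + 0.40 × 0.10 = 0.64 | 5.6% | 5.9% |
| 0.25 | 0.60 + 0.40 × 0.25 = 0.70 | 11.7% | 10.7% |
| 0.50 | 0.60 + 0.40 × 0.50 = 0.80 | 37.7% | 31.5% |

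In patients: 29 × 0.40 = 11.6 non-adopters are expected in the mHealth arm, so *f* = 0.25 means 11.6 × 0.25 = 2.9, about three patients. At *f* = 0.10 (about one patient) the error rate hardly moves.

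**The case against.** The strongest reply is that the article does not describe the harmful arrangement. It nowhere says that the individuals who coach are those who send or explain the form, or that coaches see the answers. Completion is online. A reader might infer that mHealth patients report to their own coaches and are pushed to over-report. The documents support neither statement, only that nothing stated prevents it. Nor do they say that coaching levels are set from the outcome forms: section 2.5.1.2.1 mentions weekly guidance and a diary. The low, moderate and high levels apply to adherence. For awareness only a low level is mentioned.

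Other points also stand. Medical staff hand the form to both arms, so the asymmetry lies in the coaching relationship and not in the distribution. Controls are also telephoned about adherence, so they are not free of staff contact. Coached patients know the desired answers whoever sends the link, so part of any bias would survive a change of sender. The over-reporting shares in the illustration are assumed.

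It may also be said that who sends a survey link is operational detail for the full protocol. That would carry weight if the article were silent. Section 2.8 makes an assignment, and the assignment can be improved. The general access controls and the general limitation in the Discussion do not address a difference between arms.

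**Conclusion.** The point holds as a risk left open, not as a demonstrated flaw. The article assigns distribution and explanation of the self-report forms to the professional group that coaches one arm, with evaluators aware of allocation and no stated separation of roles. Social desirability bias favouring mHealth therefore cannot be excluded for the behaviour primary outcome, which drives the sample size, or for the self-report secondary scales. Month 3 is the most exposed assessment.

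A reader might extend this to both primary outcomes. The scoring of the knowledge questionnaire does not support that. Nor should the 12% or 38% be read as the trial's expected error rate, or as what the fix would gain. They rest on assumed shares, no true effect and no offsetting over-reporting by controls, and they combine all coaching-related bias with the part due to the collection channel. The documents give no basis for estimating either part. The point is best classed as a cheap improvement.

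**What to change.** - In section 2.8, replace medical staff by the research staff of section 2.10.1.1, specified as persons who do not deliver the WeChat programme. This also reconciles the two sections.
- Send both arms the same link, with identical wording and instructions, from one neutral study account.
- State at the top of the form that treating staff will not see the answers.
- Restrict answer-level access to data management until each patient's Month 12 form is in, and say so in section 2.10.1.2.

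The cost is a few sentences and the access settings of the questionnaire platform. Sample size, visits and treatment are unchanged. The small downside is that coaches cannot use the trial scales to tailor advice. Section 2.10.2.1 lists self-reported questionnaires among the channels for adverse events, so the access rule should be worded to leave safety reporting intact.

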###### Expected outcomes

2.5.1.1.2

(1) Purpose: to provide patients with an initial understanding of brucellosis and its later stages.(2) Measures: physicians will provide one-on-one re-education to patients via WeChat, based on a self-designed push program and the brochure “Health Education for Brucellosis Patients” (50). The push program includes scientific articles on brucellosis-related concepts, disease processes, and case studies. The focus is on the negative outcomes of advanced brucellosis and the benefits of effective disease management. The program also emphasizes the importance and effectiveness of adopting healthy behaviors for better outcomes.

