#### Primary outcome

2.8.1

The primary outcome is the proportion of individuals adopting health behaviors and knowing rate of health knowledge.

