##### Knowing rate of health knowledge

2.8.1.2

The Brucellosis Health Knowledge Awareness questionnaire was designed based on the “National Brucellosis Surveillance Program” and tailored to the specific context of Baoding City, Hebei Province. The questionnaire includes items on awareness of brucellosis, its clinical symptoms, and modes of transmission. Participants indicated their knowledge, with correct answers marked as “aware” and incorrect or unknown answers as “unaware.”

The awareness rate for each item was calculated as the number of correct responses divided by the total number of valid respondents, multiplied by 100%. The overall knowledge awareness rate was calculated by dividing the total number of correct responses by the product of the total number of respondents and the total number of questions, then multiplying by 100%.

This questionnaire assesses health knowledge about brucellosis within the local population, providing essential information for health interventions.

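### The knowledge primary outcome is a right/wrong test completed online after discharge with no stated closed-book rule, and looking answers up is easier in the mHealth arm

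*Protocol article*

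**What the plan says.** Section 2.8.1 makes knowledge a primary outcome: "The primary outcome is the proportion of individuals adopting health behaviors and knowing rate of health knowledge".

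Section 2.8.1.2 gives content and scoring. On content: "The questionnaire includes items on awareness of brucellosis, its clinical symptoms, and modes of transmission". On scoring: "Participants indicated their knowledge, with correct answers marked as “aware” and incorrect or unknown answers as “unaware".

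Section 2.8 gives the mode of administration: "Medical staff will distribute the questionnaire via the Questionnaire Star web platform", and then "Patients will complete it online, receiving instructions either in person (during hospitalization) or by phone (after discharge"). Table 1 schedules the knowledge questionnaire at months 0, 3, 6, 9 and 12.

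On the mHealth arm, section 2.5.1 states: "Health education in the mobile health intervention group will be delivered via the WeChat platform on smartphones". The same section gives patients prompt messaging with a physician or nurse. Section 2.5.1.1.2 adds: "The push program includes scientific articles on brucellosis-related concepts, disease processes, and case studies". Section 2.5.1.2.1 describes the topic content as "in the form of articles, pictures, or videos sent to the advance WeChat group".

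On the control arm, section 2.5.2 provides discharge education, a brochure with the essential facts about the disease, and telephone follow-up. The mHealth arm also receives a printed booklet (2.5.1.1.1). Daily smartphone use and familiarity with WeChat are entry criteria for everyone (2.3.1).

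**The concern.** Of the instruments in section 2.8, the knowledge questionnaire is the one with an answer key. A correct tick counts as aware whether the patient remembered the answer or looked it up. After discharge the patient fills in the form online, and nothing stated asks for answers from memory.

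The intervention itself adds reference material and a clinician who can be messaged, and it adds them in one arm only. If patients consult what they have when they answer, the mHealth arm gains more from doing so. A primary outcome could then favour the intervention even where nothing extra has been learned. Because the bias enters with the responses, neither the analysts' blinding (2.10.1.4) nor multiple imputation (2.9) can remove it.

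**Working it through.** **No figure of the plan to reproduce.** The article gives no expected knowing rate, no SD and no look-up rate. The sample size in 2.4 rests on the behaviour rate, not on knowledge. The first step is therefore a comparison of passages, followed by an illustration under stated assumptions.

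**Step 1: access to answers during the test, arm by arm.**

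| Source | mHealth arm | Control arm |
|---|---|---|
| Printed material | Booklet (2.5.1.1.1) | Brochure (2.5.2) |
| Own smartphone | Yes, entry criterion (2.3.1) | Yes, entry criterion (2.3.1) |
| Pushed articles, pictures, videos | Yes (2.5.1.1.2, 2.5.1.1.3, 2.5.1.2.1) | Not described |
| Prompt clinician messaging | Yes (2.5.1) | Not described; telephone follow-up only |

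Print and general internet access are roughly balanced. The last two rows are the excess in the mHealth arm. The subject matter overlaps in broad terms: the test covers the disease, its symptoms and its transmission, and the push database has a disease-awareness section (2.7.2). The test items themselves are not shown.

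**Step 2: when it applies.** The intervention lasts 3 months (2.1), so month 3 is the assessment at which access to the chat is clearest. The month 0 test may be taken in hospital. Whether the chat and pushed material stay available at months 6, 9 and 12 is not stated.

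**Step 3: illustrative size.** Assumptions, none from the article except the 29 per arm of section 2.4:
- each patient's percentage correct has mean 70 and SD 15 in both arms, so there is no true effect;
- a share f1 of mHealth patients and f0 of controls look answers up, and each of them reaches at least 95%;
- two-sided 5% t-test, 29 per arm.

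Expected spurious gap ≈ (f1 − f0) × (95 − 70) points.
- 20% vs 20%: 0 × 25 = 0 points
- 20% vs 10%: 0.10 × 25 = 2.5 points
- 20% vs 0%: 0.20 × 25 = 5 points

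Standard error of the difference = 15 × √(2/29) = 3.94 points. The normal approximation to the false-positive rate is 1 − Φ(1.96 − gap/3.94) + Φ(−1.96 − gap/3.94):
- 2.5 points: 2.5/3.94 = 0.63, giving about 10%
- 5 points: 5/3.94 = 1.27, giving about 25%

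Simulation (20,000 runs, scores clipped to 0–100) agrees closely:

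| Look-up, mHealth vs control | Spurious gap (points) | False-positive rate |
|---|---|---|
| 20% vs 20% | 0 | 5% |
| 20% vs 15% | 1.3 | 6% |
| 20% vs 10% | 2.5 | 9% |
| 30% vs 20% | 2.5 | 9% |
| 30% vs 10% | 5 | 21% |
| 20% vs 0% | 5 | 23% |

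What matters is mainly the difference in look-up between the arms, not its overall level.

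**The case against.** The strongest objection is that this rests on silence in a condensed article. Data are collected by trained staff under operating procedures that are not shown (2.10.1.1), and a closed-book sentence could well sit there or in the form itself. That stands as a limit on confidence. It does not remove the point, because the article does describe how the questionnaire is given, and that mode, followed as written, leaves the test open to look-up.

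A reader might go further and infer four things that the documents do not support:

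- **That the test is unsupervised and taken on the phone that holds the teaching material.** Section 2.8 names a web platform and no device, and does not say whether staff stay in contact during completion. Daily smartphone use makes the phone likely, but that is inference.
- **That only the mHealth arm can look answers up.** Controls have a brochure and smartphones. The teaching material comes from sources such as WeChat, Wikipedia and doctor question-and-answer platforms (2.7.1), so similar content is open to them too. What remains is easier access in one arm.
- **That a false-positive rate of 23% is to be expected.** That figure sets control look-up at zero. With 10% look-up in controls it falls to about 9%, and with equal look-up it is the nominal 5%.
- **That the bias runs unchanged to month 12.** Continued access after month 3 is not stated.

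The Discussion concedes bias in self-reported data, but for health behaviours and self-management practices. It does not mention look-up on the knowledge test.

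**Conclusion.** The point holds in limited form. A primary outcome with an answer key is completed online after discharge, no closed-book rule is stated, and the intervention gives one arm extra material and a clinician to ask. The between-arm difference can therefore mix retained knowledge with access to reference material, most clearly at month 3.

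Whether this happens, and by how much, cannot be computed from the article. The range from 0 points and 5% to about 5 points and 23% depends entirely on the assumed mean, SD, look-up shares and score after look-up. It shows that a modest difference in look-up would matter with 29 patients per arm; it does not estimate the bias. The change is worth making because it is cheap before testing and the problem cannot be corrected in the analysis.

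**What to change.** In section 2.8:

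1. Place the knowledge items first in the online form.
2. Give the same instruction in both arms, on screen and in the phone script: answer from memory, without consulting materials, the internet, the WeChat group or other people.
3. Tell the mHealth physicians and nurses not to answer test items while a patient's questionnaire is open.
4. Name residual look-up on the knowledge test among the limitations, since compliance cannot be verified.

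The cost is a form setting, a sentence on screen, a sentence in a call that is already planned, and a note to the clinicians.

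Two alternatives are less suitable. Keeping staff on the line during the test would bring in people who may know the allocation (evaluators do, per 2.2) and who could prompt or clarify differently by arm. A time limit may penalise slow or low-literacy readers, and section 2.8.1.2 does not make clear how blanks are scored: unknown answers count as unaware, but the item rate is taken over valid respondents.
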